In sum, the potential clinical value of this research is noteworthy since it may allow screening people at risk of developing AN [18, 34]. The aforementioned research has placed a great focus on clinical and recovered AN samples. Nevertheless, there is a call to focus not only on AN samples, but also including diverse samples such as other ED subtypes [18]. According to this transdiagnostic perspective, it would be possible to find potential biomarkers or endophenotypes to identify "particular symptoms across heterogeneous illness profiles” [18]. In this context, it is not yet known whether these eye movement patterns start to manifest also in heterogeneous samples with subclinical ED symptomatology. Furthermore, studies using subclinical ED samples could help to disentangle a possible influence of starvation (which presumably is less extended under this population than in clinical ED) on these eye-movement patterns and shed light on whether these eye movement abnormalities may be a reflection of the condition itself. On the other hand, given the relative novelty of these results, there is a call in the field to replicate this underpinning research [18, 28], as well as to standardize some of these eye movement tasks (i.e., prosaccade/antisaccade tasks) [35].

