## Methods/design

### Participants and procedure

A young adult female sample will be chosen due to the higher prevalence of EDs in this population [1, 2, 7]. Thus, the sample will comprise young adult women in the 18–25 age range. The sample procedure will be through public advertisements and social media posts (convenience sampling). Inclusion criteria will be: (a) normal (or corrected) visual acuity; (b) gender: women; (c) current body mass index (BMI) in the normal range according to World Health Organization (WHO) (between 18.5–24.9). Exclusion criteria: (a) self-reported lifetime history of significant brain injury, neurological condition, ocular and/or visual pathology; (b) self-reported lifetime history of an ED or other mental illness; (c) self-reported current use of psychotropic drugs (e.g., antidepressants) or intake of recreational synthetic or natural drugs; (d) incomplete data collection or eye-tracker calibration failure; (e) inability to understand Spanish; (f) out of range age. The Spanish Eating Disorder Examination Questionnaire (S-EDE-Q) [36] will be administered since it is considered the gold standard for assessment of ED pathology [37]. The EDE-Q have shown good predictive as well as concurrent validity [37, 38]. Further, has been shown good psychometric properties in young adults in Spain [36]. This tool will serve as a pre-screening tool, allowing us to split the sample into two groups of participants with subclinical ED symptomatology and control participants according to their EDE-Q score, as defined by the study criteria (see below). A global EDE-Q score ≥ 2.8 has been shown to provide an optimal trade-off between sensitivity and specificity when it is used for screening in primary care [38]. The pre-screening will allow to form two groups of similar size: once the desired participant sample size has been reached for one of the groups, only participants falling into the other group defined for the study will be invited to take part.

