### Sample size calculation

An 80% of power analysis and a significant criterion of α = 0.05 were set since these are considered a convention for general use specifically in the psychology field [41, 42]. Regarding the effect size, based on previous literature on the topic [34], we choose a large effect size (d = 0.8) [41]. Thus, a priori t-test G*Power v3.1.9.2 (Dusseldorf University, Germany, http://www.gpower.hhu.de/en.html) analysis yields a minimum sample of 26 participants in each group (N = 52, two groups: participants with subclinical ED symptomatology vs. control participants). Nevertheless, if significant results were not obtained after completion of the study, a retrospective power analysis will be carried out with the participants responses to verify whether the non-significant result is due to lack of relationship between the groups or due to lack of statistical power. In this case, more participants will be recruited.

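### The 80% power is conditional on d = 0.8, which the protocol does not justify for a subclinical-versus-control contrast, and a null result has no sound reading rule

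*Protocol article*

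**What the plan says.** In the protocol article, Sample size calculation sets the design parameters ("An 80% of power analysis and a significant criterion of α = 0.05 were set") and takes the effect from earlier work: "based on previous literature on the topic [34], we choose a large effect size (d = 0.8". From these the "analysis yields a minimum sample of 26 participants in each group (N = 52, two groups: participants with subclinical ED symptomatology vs. control participants"). No reason is given why that effect should carry over to this sample, and no power is shown at any other effect size.

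The Background cites the same reference [34] once more, saying of this line of work that "it may allow screening people at risk of developing AN [18, 34"]. The next sentence reads: "The aforementioned research has placed a great focus on clinical and recovered AN samples". It goes on to say that "it is not yet known whether these eye movement patterns start to manifest also in heterogeneous samples with subclinical ED symptomatology", and remarks of starvation, "which presumably is less extended under this population than in clinical ED". The abstract's Discussion describes the study as the first in participants with subclinical symptoms.

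Participants and procedure requires "current body mass index (BMI) in the normal range according to World Health Organization (WHO) (between 18.5–24.9") and excludes women who report any lifetime eating disorder or other mental illness. The groups are formed by a global EDE-Q score of 2.8 or more versus below.

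Two further statements govern how a null would be handled. Sample size calculation provides that, after non-significant results, a retrospective power analysis will decide between no relationship and too little power, with further recruitment in the latter case. Statistical analysis limits the reporting of Cohen's d to variables that reach significance.

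**The concern.** The effect size comes from a literature that the protocol itself places mainly in another population, while the effect in its own population is said to be unknown. A reader will take the 80% as the chance that this study detects a real subclinical difference. It is that chance only if the difference reaches about the assumed size.

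The primary aim is whether the two groups differ, so a null result would be an answer readers use. If the true difference is real but moderate, a null is quite likely. The plan then offers two poor guides to it: a retrospective power figure, and no effect size at all for the outcomes concerned. The likely misreading is that eye movement abnormalities are absent in the subclinical phase, when the data would only be imprecise.

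**Working it through.** **Inputs.** Alpha 0.05, power 80%, d = 0.8 and 26 per group with equal allocation, all from Sample size calculation. Sidedness is not stated.

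**1. The plan's own figure.** Two independent groups, t-test, noncentral t with df = 2n − 2 and noncentrality d·√(n/2). Two-sided alpha 0.05, d = 0.8 and 80% power give n = 25.52, rounded up to 26 per group. At n = 26, noncentrality is 0.8 × √13 = 2.88 and power is 80.7%. The stated N = 52 is reproduced. One-sided testing would give 21 per group and a paired test 15 pairs, so the sizing was for two independent groups and two sides.

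**2. Power of the same 26 per group at other effects.** The document gives no subclinical effect, so 0.4 to 0.7 is an assumed range.

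| d | Power, one uncorrected test |
|---|---|
| 0.8 | 80.7% |
| 0.7 | 69.7% |
| 0.6 | 56.4% |
| 0.5 | 42.4% |
| 0.4 | 29.3% |

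The smallest d with 80% power is 0.79, so there is almost no slack. Power drops below 50% only when d is under about 0.55.

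**3. Effect of the planned multiplicity correction.** Statistical analysis plans a correction for multiple t-tests without naming the method or the number of tests. As an illustration, take Bonferroni over three tests (alpha 0.05/3). At 26 per group, power is 65.8% at d = 0.8 and 26.0% at d = 0.5, and the smallest d with 80% power is 0.92.

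**4. What a null would tell.** Near zero, the 95% confidence interval for a standardised difference has half-width 1.96 × √(2/26) = 0.54 by the normal approximation, or 2.009 × √(2/26) = 0.557 with t on 50 df. An observed difference of exactly zero therefore does not exclude d = 0.5. On this approximation the upper limit falls below 0.8 only if the observed d is under 0.8 − 0.557 = 0.243.

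**5. What retrospective power would tell.** The smallest observed d that reaches p = 0.05 is also 2.009 × √(2/26) = 0.557. Power at that value is about 50%. If retrospective power is computed from the observed effect, every non-significant result returns about 50% or less. The calculation restates the p-value and cannot separate no difference from too few participants.

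**The case against.** The strongest reply is that the 80% is right as stated, since it is given for d = 0.8. That stands, so the point is missing justification and not an arithmetic error.

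A reader might infer that the true effect must be smaller here, because these women have normal BMI and no eating disorder history. The document does not establish that. Its Background reports more square wave jerks than in healthy controls not only in patients but also in weight-restored women and in sisters of people with AN, and Study objectives and hypothesis refers to state-independence. On this evidence the subclinical effect is unknown.

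A reader might also infer that d = 0.8 is an estimate from AN patients carried over unchanged. That cannot be verified. The sample and effect in reference [34] are not shown, the Background speaks of a main focus and not an exclusive one, and 0.8 carries a second citation, [41], which is also cited for the power and alpha conventions, so it may be a benchmark.

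Nor can it be said that the study will probably miss any milder effect: at d = 0.6 and 0.7 power still exceeds 50%.

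Finally, the protocol calls the study exploratory, calls 26 a minimum, and foresees that a null may reflect low power. This softens the consequence. It does not justify the effect size, and step 5 shows that the planned tool cannot make the intended distinction.

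**Conclusion.** The concern holds in a limited form. The 80% power is conditional on d = 0.8 and on one uncorrected two-sided test, and the protocol gives no basis for that effect in subclinical women. For assumed effects of 0.6 and 0.5 power is about 56% and 42%, and lower once a correction is applied. These figures rest on the noncentral t for two equal groups. The alternative effects and the count of three tests are assumptions, not values from the document.

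The practical weight lies in the reading of a null. An interval of roughly ±0.54 to ±0.56 SD around zero leaves moderate differences open. Judging such a result by retrospective power, with no effect size reported, invites the conclusion that the abnormality is absent.

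**What to change.** Leave the planned 26 per group unchanged and make these changes:

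- In Sample size calculation, state that d = 0.8 is an assumption not estimated in a subclinical sample. Add that 26 per group gives 80% power only for d of about 0.79 or more on a single uncorrected two-sided test, with about 56% at d = 0.6 and 42% at d = 0.5. Say that power is lower after the multiplicity correction, for example 66% at d = 0.8 with Bonferroni over three tests, and replace that example once the correction and the number of tests are fixed.
- In Statistical analysis, report the effect size and its 95% confidence interval for every outcome, significant or not.
- Replace the retrospective power analysis as the guide to a null. Read a non-significant result by its confidence interval, as a difference as large as d = 0.8 not having been shown, and give the range of differences that remains compatible with the data. Do not read it as absence of the abnormality.

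The cost is a less favourable stated power and slightly more reporting. The planned group sizes and the choice of tests stay as they are.

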### Statistical analysis

Statistical analyses will be performed with SPSS v.28. Normality and outliers will be checked through graphic tests such as QQ plots, histograms, and box plots. Cronbach’s α for each questionnaire will be reported. Group analyses will be performed with Student's t-test paired comparison (for normal distribution) or Wilcoxon tests (for non-normal distribution). We will apply a correction for multiple t-test comparisons. Cohen’s d will be reported for variables showing significance. In case of significant differences between study groups, we will then include confounding variables (premorbid intelligence and anxiety) as covariates in the analysis described above. Across groups, exploratory Pearson's correlation analyses will also be conducted between S-EDE-Q, STAI scores, and BMI and the outcome measures associated with the eye-tracking data (see Table 1, for a detailed view). Additionally, if significant differences are found between STAI scores and SWJ rate, consistent with previous literature [31, 32], a discriminant analysis will be performed on the entire sample to elucidate to what extent both measures correctly classify group membership (participants with subclinical ED symptomatology vs. control participants). Alpha will be set at 0.05 for all analyses.

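### A non-significant result leads to a retrospective power check that cannot do its job, then to extra recruitment with no limit and no alpha adjustment

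*Protocol article*

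**What the plan says.** The section on sample size calculation in the protocol article sets 80% power, alpha 0.05 and a large effect (d = 0.8), and arrives at 26 per group, 52 in all. It then adds a rule for the event that the finished study shows nothing significant. Under that rule, "a retrospective power analysis will be carried out with the participants responses to verify whether the non-significant result is due to lack of relationship", as opposed to insufficient power. The rule ends with the sentence "In this case, more participants will be recruited".

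The rule does not name the outcome whose non-significance sets it off. It also gives no power level that counts as too low, no number to add, no maximum, no limit on repeats and no adjustment of alpha.

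The section on statistical analysis states "Alpha will be set at 0.05 for all analyses". It promises a correction for multiple t-test comparisons, method not named, and does not mention repeated testing after added recruitment. It also says that Cohen's "d will be reported for variables showing significance", so outcomes without significance are not promised an effect estimate.

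**The concern.** Two faults combine. First, the check is asked a question it cannot answer. For a given sample size, power computed at the observed effect is the p-value on another scale. A large p-value always gives low observed power, so the result looks most underpowered exactly when the data show least difference.

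Second, the extra participants are recruited because the first test failed, and the enlarged sample is tested again at 0.05. Each outcome then has more than one chance of a false positive at the full level, and 0.05 is no longer the error rate.

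The study states directional hypotheses and offers its findings as a starting point for later work on biomarkers, so a false positive would be carried forward. Reporting d only for significant outcomes also withholds the quantity that could show whether a null result is informative.

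**Working it through.** **Inputs.** From the sample size section: n = 26 per group, d = 0.8, alpha 0.05, power 80%. From the statistical analysis section: alpha 0.05 for all analyses and a multiplicity correction across t-tests. Assumed, because the article does not give them: a two-sided independent-groups t-test, the size and number of extensions, and the form of the correction.

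**1. The plan's own figure.** Power = P(|T| > t(0.975, 2n-2)), with T noncentral t and noncentrality d·√(n/2). At d = 0.8, n = 25 gives 79.1% and n = 26 gives 80.7%. The stated 26 per group reproduces with a two-sided test (a one-sided test would need 21). The initial sample size is not in error.

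**2. Observed power.** The observed effect is d = t·√(2/n). Putting it back into the noncentrality gives d·√(n/2) = t, so observed power depends only on t, hence only on p. With 50 degrees of freedom:

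| p | observed d | observed power |
|---|---|---|
| 0.05 | 2.009 × √(2/26) = 0.557 | 50.4% |
| 0.10 | 0.465 | 37.6% |
| 0.20 | 0.360 | 24.7% |
| 0.50 | 0.188 | 10.2% |

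The ceiling of about 50% at p = 0.05 does not move with sample size (50.3% at 39 per group, 50.1% at 104). No result with p > 0.05 can reach 80%.

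**3. Type I error after one extension, one outcome at 0.05.** Under no difference, the test statistics at n1 and n2 per group have correlation √(n1/n2). The error is P(|Z1| > 1.96 or |Z2| > 1.96).
- 26 to 36 per group: correlation √(26/36) = 0.850, error about 7.5%.
- 26 to 52 per group: correlation √(26/52) = 0.707, error 8.3%.

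Repeated simulations with t-tests gave 7.4-7.7% and 8.0-8.5% for these two cases.

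**4. If the step were repeated (illustration only).** Five extensions gave about 13-14% in steps of 10 per group and about 15-16% in steps of 26.

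**5. With a multiplicity correction.** Table 1 lists 18 outcomes: 1 for fixation, 5 for prosaccade, 7 for antisaccade and 5 for memory-guided saccade. An assumed Bonferroni level is 0.05/18 = 0.0028 per outcome. One doubling from 26 to 52 per group raises the per-outcome error from 0.28% to about 0.5%, a ratio of about 1.8 (0.5/0.28). The uncorrected ratio is 8.3/5, about 1.7.

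**6. An adjusted level.** For two equal looks (26, then 52 per group), a critical value of z = 2.178, or a nominal two-sided 0.0294 at each look, returns the overall error to 5%. Simulation with t-tests gave 4.9%.

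**7. What an interval can show.** The 95% CI for d is roughly d ± 1.96·√(2/26 + d²/(4 × 26)). At observed d = 0 it is ±0.54, which excludes 0.8. At d = 0.25 the upper limit is 0.25 + 0.546 = 0.796; at d = 0.26 it is 0.26 + 0.546 = 0.806. So the interval excludes 0.8 only for observed d below about 0.26. From there up to 0.557, where significance begins, it contains both 0 and 0.8.

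**The case against.** The strongest reply is that the article describes one check and one response. A reader might infer recruitment that goes on until significance is reached. The text describes no such loop, and the 13-16% figures depend on five extensions that it never mentions. That stands: those figures show only what the absence of a limit permits, and the single-extension figure is the one to use.

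A reader might also infer that the check must fire every time. This is conditional. If power were recomputed at the planned d = 0.8, it would be 80.7% whatever the data showed. The wording points to the participants' own responses, though, and a figure fixed in advance could not explain a null result either. Power from the observed SD and a fixed raw difference is a further possibility and would not be a function of p alone, but the article does not describe it. If tests used a Bonferroni level over 18 outcomes and the power check used 0.05, results with p between about 0.0028 and 0.0062 would show 80-87% power and would not fire. These are narrow or unstated readings. If the sentence on further recruitment refers simply to non-significance, extension follows without any check.

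Third, the planned multiplicity correction makes the per-outcome errors much smaller than 5-8%. This stands for the absolute figures, not for the relative inflation: a correction across outcomes does not cover repeated looks. The single-outcome calculation also does not model a trigger defined as no outcome being significant, and the article does not say which trigger it means.

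Finally, the study calls itself exploratory, and an analysis plan may exist elsewhere. But it states directional hypotheses with a power target and an alpha, and the point concerns a rule that the article lays down, not a detail left out.

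**Conclusion.** The point holds. As written, the retrospective check cannot separate absence of a relationship from lack of power, and on the natural reading it will practically always favour extension. The added recruitment and retesting then make the stated alpha of 0.05 untrue.

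The size is moderate. It is about 7.5-8.4% instead of 5% for one outcome tested at 0.05 with one extension of 10 to 26 per group, and about 0.5% instead of 0.28% under an assumed Bonferroni correction over 18 outcomes. Extension size, number of looks and form of correction are assumptions. The article supports neither a claim that recruitment will continue until significance nor an error rate of 13-16% for this study.

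Reporting d only for significant outcomes is a separate weakness. It matters here because it removes the estimate needed to interpret a null result; the extension rule does not cause it.

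**What to change.** Delete the retrospective power analysis. Then choose one of two equally acceptable courses:

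- **(a)** Fix the sample at 26 per group and remove the sentence on recruiting more participants.
- **(b)** Pre-specify a single extension with a named trigger outcome, a maximum N and an adjusted alpha, for example 0.0294 at each of two equal looks, applied within the multiplicity correction.

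Under either course, report the mean difference and Cohen's d with a 95% CI for every Table 1 outcome, significant or not. State in advance that a non-significant result is read from the interval. With 26 per group, an observed d below about 0.26 excludes the planned effect of 0.8; a larger non-significant d is called inconclusive.

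The cost is a change of wording and extra table columns. Under (a) the sponsor gives up the open-ended option to extend; under (b) it accepts a somewhat stricter alpha at each look. Some null results will remain inconclusive, and the plan should say so.

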### Statistical analysis

Statistical analyses will be performed with SPSS v.28. Normality and outliers will be checked through graphic tests such as QQ plots, histograms, and box plots. Cronbach’s α for each questionnaire will be reported. Group analyses will be performed with Student's t-test paired comparison (for normal distribution) or Wilcoxon tests (for non-normal distribution). We will apply a correction for multiple t-test comparisons. Cohen’s d will be reported for variables showing significance. In case of significant differences between study groups, we will then include confounding variables (premorbid intelligence and anxiety) as covariates in the analysis described above. Across groups, exploratory Pearson's correlation analyses will also be conducted between S-EDE-Q, STAI scores, and BMI and the outcome measures associated with the eye-tracking data (see Table 1, for a detailed view). Additionally, if significant differences are found between STAI scores and SWJ rate, consistent with previous literature [31, 32], a discriminant analysis will be performed on the entire sample to elucidate to what extent both measures correctly classify group membership (participants with subclinical ED symptomatology vs. control participants). Alpha will be set at 0.05 for all analyses.

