### Study objectives and hypothesis

As Malcom and Phillipou [18] noted in their recent review, demonstrating a relationship with illness is one of the first steps in determining biomarkers and endophenotypes. As illustrative example, first Phillipou et al. [33] showed the existence of specific eye movement anomalies in patients with AN and only after these findings, they amplified the scope of their study and were able to identify the state-independence of these eye movement abnormalities [32]. Following this line of reasoning, we will investigate whether the aforementioned eye movement abnormalities detected are, in this case, associated in young-adult women with subclinical symptomatology. Therefore, this study will take as primary aim to investigate whether participants with subclinical ED symptomatology and control participants differ in their performance on a range of eye movement tasks. We hypothesize that participants with subclinical ED symptomatology compared to controls would be prone to show shorter saccade latencies and more inhibitory errors in a prosaccade/antisaccade task and in a memory-guided saccade task, respectively, and an increased rate of SWJs in a fixation task. Additionally, as secondary aim, and following the same approach of Phillipou et al. [31, 32], we will test the potential role of SWJ rate and anxiety for discriminating the different groups tested in our study (participants with subclinical ED symptomatology vs. control participants).

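### A paired t-test is specified for two unmatched groups of different women, so the p-value for the primary aim would depend on arbitrary row order

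*Protocol article*

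**What the plan says.** All references are to the protocol article.

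- **Statistical analysis:** the group analyses use Student's "t-test paired comparison (for normal distribution) or Wilcoxon tests (for non-normal distribution"). If groups differ significantly, premorbid intelligence and anxiety are then added as covariates to that same analysis.
- **Participants and procedure:** the EDE-Q is the pre-screening tool, "allowing us to split the sample into two groups of participants with subclinical ED symptomatology and control participants according to their EDE-Q score". Recruitment is by quota: "once the desired participant sample size has been reached for one of the groups, only participants falling into the other group" is invited. The stated result is only approximate balance: "The pre-screening will allow to form two groups of similar size".
- **Study objectives and hypothesis:** the primary aim is to find out "whether participants with subclinical ED symptomatology and control participants differ in their performance on a range of eye movement tasks".
- **Sample size calculation:** "An 80% of power analysis and a significant criterion of α = 0.05 were set", and "we choose a large effect size (d = 0.8"), giving "a minimum sample of 26 participants in each group" and 52 in total.

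**The concern.** A paired test needs a defined link between each observation in one group and one observation in the other, such as the same person measured twice or an individually matched control. This design has neither. Each woman contributes to one group only, and no matching rule appears anywhere in the article. The sentence concerns the group analyses, so it cannot be read as referring to a within-person contrast.

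This is the only test named for the primary aim, and its significance steers later steps. Covariates are added only after a significant group difference, the discriminant analysis depends on significant findings, and a non-significant result leads to further recruitment. An analyst who follows the text in SPSS would select the paired-samples procedure, which pairs whichever values share a row.

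**Working it through.** **Inputs.** From Sample size calculation: d = 0.8, power 80%, α = 0.05, 26 per group. Sidedness is not stated. From Participants and procedure: two unmatched groups. The data sets in step 3 are simulated for illustration and are not trial data.

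**1. Reproduce the plan's figure with an independent-samples test.**
- Normal approximation: n = 2(z₀.₉₇₅ + z₀.₈₀)²/d² = 2(1.960 + 0.842)²/0.64 = 24.5, so 25 per group.
- Exact (noncentral t), two-sided: 25.52, so **26 per group**. Power is 80.7% at 26 and 79.1% at 25.
- Exact, one-sided: 21 per group.

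The stated 26 matches the two-sided independent-samples t-test exactly.

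**2. The same inputs with a paired test.**
- If 0.8 is the standardised mean of the pair differences (dz), 14.30, so 15 pairs.
- If the pairs are unrelated people, the SD of a difference is σ√2, so dz = 0.8/√2 = 0.566. The requirement is 26.51, so 27 pairs.

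Neither gives 26. With unrelated pairs the noncentrality is unchanged: 0.566 × √26 = 2.884, against 0.8 × √(26/2) = 2.884. Only the degrees of freedom change, from 50 to 25, and power falls from 80.7% to 79.2%.

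**3. Dependence on row order.** With 26 per group and equal SDs,

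t(paired) = t(independent) / √(1 − r),

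where r is the sample correlation that the chosen row order happens to produce. Under random ordering r has mean 0 and SD 1/√(26 − 1) = 0.20, so its central 95% range is about ±0.39.

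For an independent p of 0.030 (t = 2.234 on 50 df):
- r = +0.39: t = 2.234/√0.61 = 2.860 on 25 df, p = 0.008
- r = −0.39: t = 2.234/√1.39 = 1.895 on 25 df, p = 0.070

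Simulated re-pairings of fixed data sets agree:

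| Independent p | Paired p, central 95% | Share of orders with p < 0.05 |
|---|---|---|
| 0.030 (20,000 orders) | 0.0085 to 0.070 | 81% |
| 0.049 (observed d = 0.56; 10,000 orders) | 0.017 to 0.100 | 44% |

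In the second data set the most extreme random orders gave p = 0.0025 and p = 0.133. Sorting both columns by outcome gave p = 7 × 10⁻⁷, and sorting them in opposite directions gave p = 0.16. The signed-rank test (2,000 orders) ranged from 0.004 to 0.45.

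**4. Average error rates (100,000 simulated trials, 26 per group).**
- Random row order: type I error 5.0% paired and 5.0% independent; power at d = 0.8 is 79.1% paired and 80.7% independent.
- Both columns sorted by outcome before pairing: type I error about 65%.

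**5. Fit with the rest of the analysis section.** Premorbid intelligence and anxiety belong to the individual woman. Neither a paired t-test nor a Wilcoxon test can take them as covariates in the way described, whereas an independent-groups linear model can. If exclusions leave the groups unequal, a paired test also cannot use everyone.

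**The case against.** The strongest reply is that the word paired is a slip for pairwise or two-group. The sample size, the primary aim and the covariate step all describe an independent-groups comparison, so the analysts may well intend the correct test. That is plausible, but nothing in the article corrects the wording, and a reader cannot confirm the intent.

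Other points on that side hold in part:
- **Wilcoxon.** The name covers both the signed-rank and the rank-sum test, and the rank-sum test is valid here. Beside the word paired it reads as signed-rank, but this part is ambiguous, not plainly wrong.
- **Small average harm.** With random row order the type I error is not inflated and power falls by about 1.5 points. The loss of degrees of freedom is already inside that figure. The 65% error rate needs rows sorted by outcome, which nothing in the article suggests.
- **The 15-pair contrast.** It takes dz equal to d. For unrelated people the paired requirement is 27, close to 26. The exact match to the independent-samples calculation is the better evidence.
- **Unequal groups.** These are possible, not planned: the target is 26 in each group, and recruitment to a group closes once it is full.

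**Conclusion.** The concern holds: the test as written is wrong for this design and contradicts the article's own sample-size calculation. It must be corrected before analysis, because it governs the primary comparison.

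The damage is an arbitrary p-value, with no appreciable loss of power or average error control when row order is random. In the two illustrative data sets, a result near the 5% threshold could fall on either side of it through row order alone: 19% of orders lost significance when the independent p was 0.030, and 56% (100 − 44) when it was 0.049. These shares depend on the simulated data and on how close the result lies to the threshold. The contradiction itself rests only on the article's text and on the exact reproduction of 26 per group, assuming a two-sided test.

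**What to change.** Replace the sentence in Statistical analysis with wording such as: *Between-group comparisons will use the independent-samples t-test (Welch) or, for non-normal outcomes, the Mann-Whitney U (Wilcoxon rank-sum) test.* Removing the pairing is the essential change. Student's independent-samples t-test would also cure it; Welch's version additionally avoids assuming equal variances.

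State in the same place that the covariate-adjusted comparison will use ANCOVA or linear regression with group as a factor, since neither of the tests above can carry covariates.

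The cost is a change of wording. The 26 per group still supports the t-test at 80.7% power. If an outcome is normal but analysed by the rank-sum test, the requirement is about 25.52/(3/π) = 26.7, so 27 per group.
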